### Outcome measures

#### Primary implementation outcome

Table 3 lists the study implementation outcomes. For the primary implementation outcome, the proportions of outpatients screened on the PHQ-2 by the ANM/nurse will be compared between study arms. The denominator for the proportion of outpatients screened will be calculated as the total number of adult outpatients for the NCD care program attending the PHCs during the trial period. ANMs/nurses will use a Screening Record Register to document the number of patients screened. The facilities will send the screening data to the data manager on a weekly basis.

**Table 3 T3:** Implementation outcomes.

Measure	Source	Description	Rationale for selection	Hypothesis	Timeline
Primary outcome					
Comparison of Proportion of persons screened on PHQ-2	Screening record register data on primary health center implementation activities, filled regularly by the ANM/nurse	The percentage of adult individuals attending primary health centers who are screened on PHQ-2 by the ANM/nurse.	Screening for depression on PHQ-2 is the gateway for initiating depression care.		Collected/reviewed weekly over the trial duration
Secondary outcomes					
Acceptability: Proportion of patients who refuse to be screened for depression	Screening Record Register data on primary health center implementation activities, filled regularly by the ANM/nurse	The percentage of adult individuals attending primary health centers who refuse to be screened on PHQ-2 by the ANM/nurse will be compared between the trial arms.	Screening for depression on PHQ-2 is the rate-limiting step in the entire patient flow at a primary health center, therefore, assessing the extent of refusal of being screened is important for understanding the acceptability of implementation of depression screening.	The proportion of persons who refuse to be screened on PHQ-2 will be significantly lesser in the intervention arm or in facilities receiving enhanced implementation support, than those receiving routine support (control arm)	Collected/reviewed weekly over the trial duration
Adoption: Proportion of patients initiated on treatment	Screening Record Register data on primary health center implementation activities, filled regularly by the ANM/nurse	The percentage of adult individuals attending primary health centers who are screened positive on PHQ-2 by the ANM/nurse, referred to the MO and initiated on treatment by the MO i.e., provision of psychoeducation and appropriate antidepressant medication and/or referral to the Healthy Activity Program delivered by the ASHA worker, and/or referral to a specialist at the District Mental Health Program or Community Health Centre or private clinic.	Treatment initiation by the medical officer is a comprehensive process indicator as it covers the preceding steps in the patient flow at a primary health center. In addition, this measure reflects the downstream effect of implementation support strategies on adoption of collaborative care package for depression care.	The proportion of screened positive cases initiated on treatment will be significantly greater in the intervention arm or in facilities receiving enhanced implementation support, than in the control arm or in facilities receiving routine support.	Collected/reviewed weekly over the trial duration
Appropriateness, Feasibility, Fidelity (Qualitative measures)	Post-trial exit interviews and/or focus groups with medical officers, ANMs/nurses	Interviews and/or focus groups will discuss experiences of suitability of the integration of mental health services with routine primary care (both arms), practical challenges in achieving the same and extent of adherence to the implementation protocols; Additionally, in the intervention clusters, the discussion will also focus on suitability of the implementation support coaching process as perceived by the facility team, their experiences and challenges of coaching and the extent to which they could adhere to coaching guidance.	Based on Proctor's framework (2010) and the given measures as well as to increase efficiency of resources and time, we have considered a qualitative approach to data collection that we will deploy after completion of trial activities.	Appropriateness, Feasibility and Fidelity of integration of mental health services into routine primary care will be greater in the intervention arm compared to control arm as assessed qualitatively; Within the intervention arm, the appropriateness, feasibility and fidelity of implementation support coaching will be optimum as assessed qualitatively.	End of the study
Cost of Enhanced implementation support: strategy development and delivery costs	Primary health center Facility records; Sangath-Bhopal administrative and finance department for Enhanced Support arm	With regards to development costs, we will include costs for developing Enhanced Implementation Support Strategy (EISS), training the coaches, and piloting/embedding the EISS before formal implementation in the definitive trial. We will capture the costs related to (1) human resources required for developing the EISS, including involved personnel's responsibility, time spent, and salary or payment received, (2) information technology used for development of EISS (e.g., laptops, internet bills, any software etc.), and (3) infrastructure related support such as office supplies, rent, utility etc. Data will be captured via time logs, payrolls etc. by a member of the trial team on a monthly basis. With regards to measuring costs of implementing EISS at seven primary health centres (intervention arm), we will capture spending on (1) health workforce for implementing the EISS (e.g., costs of time spent on coaching facility staff and facility staff's time spent on implementing the EISS-related activities that would enhance their depression screening), (2) technology related costs of coaching (e.g., internet costs, phone bills etc.).	Based on WHO's health system building blocks (WHO, 2010).	Data only collected in the intervention arm	Data will be collected bi-weekly from the beginning of embedding period until the end of the intervention delivery period of the trial.
Exploratory outcomes					
Facility readiness scores and predictors of adoption of collaborative care package for depression	Health Facility Context Assessment (Atlas Initiative Context Assessment Tool, Ariadne Labs), which includes the ‘progress’ survey and the ‘post-implementation’ survey	We have adapted the Atlas toolkit and will use the *Progress* and *Post-Implementation* surveys for trial requirements. The *Progress survey* for frontline staff and facility-leader (medical officer) is a 57-item tool, and *post-Implementation survey* is a 55-item tool. The target audience of these two surveys will include leaders, such as facility-level medical officers in-charge, and frontline healthcare workers involved in delivering the intervention such as ANMs/nurses. Implementation strategy and therefore, look at facility-level factors that are more dynamic than those in the Foundation Survey. The target audience will be similar to that of the Foundation Survey.	In a nutshell, the Progress Survey taps the internal culture of the organisation, which is not expected to change soon after the roll out of the implementation support strategy. The Post-Implementation Survey will assess the need for modifications to the implementation support strategy. The “Progress” Survey will aim to assess the key contextual factors that impact the implementation of a healthcare intervention and should be considered when making decisions about the readiness to implement, the implementation strategy, and possible adaptations to the designed intervention before its delivery. 2. The “Post-Implementation” Survey: The Launch Survey will examine the need to make modifications to the implementation strategy and therefore, look at facility-level factors that are more dynamic than those in the Foundation Survey.	Facilities that show greater readiness scores (regardless of arm allocation) will show greater adoption of the depression care program, resulting in improved implementation outcomes.	The Progress survey will be administered towards the end of embedding as a baseline. The Post-implementation survey will be administered about a month before wrap-up of trial activities.
	The Organizational Readiness for Implementing Change (ORIC) survey	The Organizational Readiness for Implementing Change (ORIC) will be used to assess readiness of the PHCs for implementation of the depression care package.	This 12-item survey is based on Weiner's theory of organizational readiness for change and covers two core constructs—change commitment (5 items) and change efficacy (7 items).	Facilities that show greater readiness scores (regardless of arm allocation) will show greater adoption of the depression care program, resulting in improved implementation outcomes.	This survey will be administered towards the end of embedding as a baseline, and about a month before wrap-up of trial activities.

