The teams at all 14 PHCs were trained on the World Health Organization's (WHO) mhGAP intervention guide (5), previously adapted for Sehore district (14). The MOs were trained through in-person and virtual modes, depending on their availability to attend in-person training, over eight days in the diagnosis, treatment and referral of positive cases of depression, including the option for referring patients to receive HAP delivered by ASHAs (29). The training for ANMs and nurses was conducted separately, as part of a 2-day in person training with instruction on screening of outpatients for depression, and referral and tracking of depression cases. Training for ANMs and nurses emphasized case detection and screening outpatients using the PHQ-2, and entering data into a “Screening Record Register” to track screening rates, refusal, patient willingness to be contacted by the research team (to participate if they screen positive), and referral to the MO and initiation of treatment. The PHQ-2 is a screening questionnaire for depression which comprises two items of the widely used and contextually validated PHQ-9. The PHQ-2 was selected to increase the quality and efficiency of screening conducted by ANMs/Nurses, and its use, instead of the full 9 item version, is supported by prior studies showing that the positive predictive value for the presence of “any depressive disorder” is 75% for a score of ≥3 (38). Further, the health system in India has planned to adopt the PHQ-2 for community-level depression screening (39). Each trial arm will have 7 PHCs, with estimated total staffing of 14 MOs (2 per facility), 14 nurses (2 per facility), and 7 ANMs (1 per facility), with some variation in staffing expected between facilities.

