Components of support	Mental health data will be reviewed as part of the usual NCD review process. This may include: - Weekly in person facility meetings to review and discuss mental health and other performance indicators - Monthly mental health performance indicator data received by facilities via email - Data submission reminders from District Level team to facilities via common WhatsApp group	Mental health data will be reviewed as part of the usual NCD review process. This may include: - Weekly in person facility meetings to review and discuss mental health and other performance indicators - Monthly mental health performance indicator data received by facilities via email - Data submission reminders from District Level team to facilities via common WhatsApp group In addition, the Enhanced Implementation Support Strategy includes: (1) **Technical assistance** remote coaching sessions delivered by ESSENCE Implementation Coaching Support team to review depression screening performance indicator data with facility team *(every two weeks)* (2) Cross-facility **collaborative virtual learning conferences** moderated by ESSENCE Implementation Support Team *(planned monthly)* (3) Cross-facility WhatsApp group for **remote peer-to-peer collaborative learning** moderated by ESSENCE Implementation Support team *(throughout intervention)*

**Table 2 T2:** Indicators of successful integration of depression care.

List of indicators collected from all facilities
1. Proportion of patients screened on PHQ-2
2. Proportion of patients who refused PHQ-2 screening
3. Proportion of patients screened positive on PHQ-2 (scored ≥3) or “cases”
4. Proportion of cases who agreed to be called by the Research Assistant (“assent”)
5. Proportion of cases referred for MO consultation
6. Proportion of cases who received antidepressant
7. Proportion of cases referred to District Mental Health Program
8. Proportion of cases referred to the ASHA for brief psychosocial intervention (i.e., HAP)
9. Proportion of cases with scheduled followed up for antidepressant medication
10. Proportion of cases who followed up for antidepressant medication
11. Proportion of cases who missed follow up for antidepressant medication
12. Proportion of cases initiated on HAP
13. Proportion of HAP follow-up sessions delivered of those scheduled
14. Proportion of loss to follow-up cases in HAP of those initiated into HAP
15. Proportion of HAP treatments closed of those initiated into HAP

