#### Secondary implementation outcomes

As outlined in Table 3, secondary implementation outcomes will be guided by the heuristic defined by Proctor et al, 2010 (19), and will be assessed using facility-level administrative data and the indicators captured in the screening record register (Table 2), and supplemented with qualitative semi-structured interviews with the facility teams. Implementation metrics will include number of patients who refuse screening, number of patients who screen positive for depression, number of screen positive patients who are referred to the MO and number of patients who are initiated on treatment. Treatment initiation following referral to the MO is an important adoption outcome, and can involve provision of psychoeducation, prescription of antidepressant medication, referral to the brief psychosocial intervention (i.e., HAP) delivered by ASHAs, and/or referral to a specialist at the District Mental Health Program, Community Health Centre or private clinic.

The costs of delivering the Enhanced Implementation Support strategy in the intervention arm PHCs will be collected and categorized into the six building blocks of a health system based on the WHO's health system framework (45). This will include spending on health workforce for participating in the Enhanced Implementation Support strategy activities, such as time required to moderate (for the coaches) and participate (for the ANM/nurse) in the coaching sessions; and information technology, such as internet costs or phone bills for engaging in the coaching sessions. This data will be captured via time logs, payroll, and expense reports. Facility staff salaries will be collected from the National Health Mission reports on salary range for various health personnel in public health facilities. To clarify, the cost analysis will not evaluate the cost-effectiveness or involve a comparison of costs between the study arms because we are not able to collect cost data from the control arm given the irregular or need-based format of routine district team's support to the clinics for delivering depression care (refer, “Routine implementation support”), and because there is no additional implementation support being provided by our team for which the costs could be collected. We will be assessing only the cost of delivery of Enhanced Implementation Support strategy among the intervention arm clinics.

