### Sample size estimation

Based on prior outpatient footfall data from participating PHCs, it is estimated that roughly 178 adult outpatients will attend each PHC per month; thus, over a 12-month period of delivery of the Enhanced Implementation Support strategy, there will be approximately 14,994 patients attending facilities in each arm. Assuming about 10% of these patients [based on prior case detection data in the region (14)] will refuse screening or will be excluded at the discretion of the ANM/nurse, the resulting estimates work out to about 13,494 outpatients available for screening in each arm. This sample size will allow us to detect a 15% difference in the proportion of PHQ-2 screenings between arms, assuming that 10% of patients are screened in the Routine Implementation Support Arm, at 80% power, an inter-cluster coefficient of variation of 0.5 (calculated from background facility data on adult outpatient footfall and existing NCD screening rates) and an intra-cluster correlation (ICC) of 0.05 (52).

Proportions (and not numbers of screenings) will be used to account for the between-facility variation in outpatient footfall.

The earlier PRIME study conducted in the same region achieved a 12% depression screening rate in its facility detection survey component (14), and assuming an additional contribution by the various components of enhanced implementation support (i.e., fortnightly coaching calls, WhatsApp support and monthly peer-learning conferences) to further increase the depression screening rate, we will hypothesize a 25% screening rate in the intervention arm, or a 15% between-arm difference in screening rates. We have referred the formula for calculating sample size for parallel cluster randomized controlled trials with fixed number of clusters (*n* = 14 in this study) by Hemming et al. 2020 (52).

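### Acceptability is defined as refusals per attendee, which mixes how many patients are asked with how many decline and biases this secondary comparison against the enhanced arm

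*Protocol article*

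**What the plan says.** In Table 3 the first secondary implementation outcome is acceptability, described as "The percentage of adult individuals attending primary health centers who refuse to be screened on PHQ-2 by the ANM/nurse", to be compared between arms. The hypothesis in the same row is directional: "The proportion of persons who refuse to be screened on PHQ-2 will be significantly lesser in the intervention arm".

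The refusal measure appears in two other places. Table 2, indicator 2, reads "Proportion of patients who refused PHQ-2 screening" and names no denominator. The section on secondary implementation outcomes speaks of a count: "Implementation metrics will include number of patients who refuse screening". Nowhere is the denominator the set of patients who were offered the PHQ-2.

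Two further statements matter. Under sample size estimation, the control arm is planned "assuming that 10% of patients are screened in the Routine Implementation Support Arm", and for the other arm "we will hypothesize a 25% screening rate in the intervention arm, or a 15% between-arm difference in screening rates". Under facility eligibility and recruitment, the Screening Record Register is said "to track screening rates, refusal, patient willingness to be contacted by the research team", among other items, so both screenings and refusals are recorded.

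**The concern.** A patient who is never asked cannot refuse. With all attendees as denominator, the outcome is the product of two things: the share of attendees who are offered the PHQ-2, and the share of those offered who decline. Only the second speaks to acceptability. The first is what the coaching is meant to change, because the enhanced strategy targets screening by ANMs and nurses.

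The primary hypothesis and the acceptability hypothesis therefore pull against each other by construction. If coaching raises screening as planned, refusals per attendee tend to rise too, even if each patient asked is just as willing as before. A facility that asks nobody scores 0%, the best possible value. At stake is the reading of a named secondary outcome: better acceptability could appear as no difference, or as worse acceptability.

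**Working it through.** **Inputs from the protocol article**
- Screened: 10% control, 25% enhanced (sample size estimation).
- Attendees per arm: 14,994; available for screening: 13,494 (same section).
- 7 facilities per arm; ICC 0.05; coefficient of variation 0.5, read here as variation in cluster size; 80% power.
- Refusal: the only planning figure is about 10% of attendees who refuse or are excluded at staff discretion. It is not split into its two parts and is the same in both arms.

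**Assumptions.** Refusal per offer, r, is not in the documents, so a range is shown. Everyone offered is taken to be either screened or to refuse.

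**The plan's own figures.** 178 × 7 × 12 = 14,952, close to the stated 14,994 (which is 178.5 × 84). 14,994 × 0.9 = 13,494.6, as stated. With m = 13,494/7 = 1,928, the design effect is 1 + ((1 + 0.5²) × 1,928 − 1) × 0.05 = 121.4, and the effective size is 13,494/121.4 = 111 per arm. A t-test on 12 degrees of freedom at two-sided 0.05 (assumed) gives power 0.787 for 10% versus 25%, in line with the stated 80%. The plan's screening rates are therefore used as given. The plan states no figure for acceptability itself.

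**Refusals per attendee.** Let s be the share of attendees screened. Offered = s/(1 − r), so refused per attendee = s × r/(1 − r). At equal r the arm ratio is 0.25/0.10 = 2.5, whatever r is. If the 10% and 25% refer to the patients available for screening instead of all attendees, both values shrink by the factor 0.9 and the ratio stays 2.5.

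The enhanced arm breaks even with control when r_E = 0.4 r_C/(1 − 0.6 r_C).

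| Assumed r, both arms | Control, per attendee | Enhanced, per attendee | Break-even r in enhanced arm | Relative fall needed |
|---|---|---|---|---|
| 2% | 0.20% | 0.51% | 0.8% | 60% |
| 5% | 0.53% | 1.32% | 2.1% | 59% |
| 10% | 1.11% | 2.78% | 4.3% | 57% |
| 20% | 2.50% | 6.25% | 9.1% | 55% |
| 30% | 4.29% | 10.71% | 14.6% | 51% |

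At r = 10% this is about 167 versus 417 refusals among 14,994 attendees per arm.

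**Unequal willingness**
- Refusal per offer halved, 10% to 5%: 1.11% versus 0.25 × 0.05/0.95 = 1.32%. A true gain reads as slightly worse.
- Refusal per offer from 10% to 4%: 1.11% versus 0.25 × 0.04/0.96 = 1.04%. The gain now reads as slightly better.
- 10% of attendees refuse in both arms (the planning figure, if all of it were refusal): the outcome reads 10% versus 10%. Per offer, refusal is 0.10/0.20 = 50% versus 0.10/0.35 = 28.6%. A large gain disappears.

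**Would a reversal reach significance?** For 1.11% versus 2.78% with 14,994 attendees per arm, the same coefficient of variation and ICC 0.05, the design effect is 134.8 and the effective size 111 per arm. Power on 12 degrees of freedom is about 13%. No ICC for refusal is given; assumed values of 0.02, 0.01 and 0.005 give about 26%, 45% and 72%.

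**The case against.** **The denominator may be loose wording.** The adoption row of Table 3 opens with the same reference to adults attending, yet its hypothesis is stated among screen-positive cases. The acceptability title and hypothesis, Table 2 and the text give no attendee denominator, and an unseen analysis plan could settle the matter. This has some force. Still, the description column is the only place where a denominator is stated, and it states attendees. Table 2 conditions on the relevant subset for several HAP indicators but not for refusal.

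**The goal is 100% screening, so attendees are nearly those offered.** The programme goal is 100%, but the sample size rests on 10% and 25%. Even if 10% of attendees refused, 80% of control and 65% of enhanced-arm attendees would be neither screened nor refusing.

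**A reader might infer that the definition defeats the hypothesis, or that the trial will report significantly more refusal under coaching.** The documents support neither. A fall in refusal per offer beyond the break-even values would still meet the hypothesis. At the planned ICC a significant reversal has only about 13% power in the 10% example. A blurred, inconclusive comparison is more likely.

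**Acceptability does not rest on this measure alone.** Staff interviews in both arms and field observation also address it, and the primary outcome is untouched. This stands and limits the severity. Refusal is nevertheless the quantitative acceptability outcome in Table 3, with a directional hypothesis attached.

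**Changing the denominator has its own risk.** Unblinded staff choose whom to approach and record the refusals, which could differ by arm. This also stands, and it is a reason to report both measures.

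**Conclusion.** The point holds as a bias in one secondary comparison and should be fixed. As written, the outcome mixes offer rate with willingness. At the plan's own screening rates, equal willingness gives a 2.5-fold higher value in the enhanced arm. For control refusal of 2% to 30% per offer, the measure favours the enhanced arm only after a relative fall of about 51% to 60%. It can hide a true gain (50% versus 28.6% per offer reading as 10% versus 10%) or reverse one (10% versus 5% per offer reading as 1.11% versus 1.32%).

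The 2.5-fold ratio depends on the planned 10% and 25% being realised and on everyone offered being either screened or refusing. The absolute percentages also depend on the assumed r.

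**What to change.** Before analysis, define acceptability as refused / (screened + refused), taken from the Screening Record Register. Report exclusions at staff discretion separately, and keep refusals per attendee as a descriptive figure. Align Table 2 indicator 2, the Table 3 description and hypothesis, and the text on secondary implementation outcomes with this definition.

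The trial status section reports closeout as complete with primary analyses to follow. Record the change, with its reason, as made after data collection but before analysis.

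No new data appear to be needed, since the register tracks both counts. The cost is a smaller denominator that depends on whom unblinded staff approach and on complete recording of refusals. Showing the two measures side by side lets readers judge that.
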